### Data management and quality control

To guarantee the consistency of the clinical trial among the institutions, all staff participating in this trial will receive training before study initiation. This training will include education about the procedures, acupuncture treatment, and outcome measure assessments.

A clinical research coordinator, trained in good clinical practice, will collect and record the study data in the CRF. To ensure confidence in the data, study-related documents including consent forms, the CRF, questionnaires, medical records, and other records will be stored in a locked space or on a password-protected computer in each hospital for 3 years after study completion.

If the protocol is revised, this will be handled by Kyung Hee University Korean Medicine Hospital as a central coordinating facility. Any protocol amendments will be reviewed and approved by the ethics committee before application in the study and published via the Clinical Research Information System (CRIS).

No formal data monitoring committee will be convened for this study. However, quality will be maintained in the study by an independent clinical research associate (CRA) who will regularly audit and monitor the study at each hospital. The CRA will monitor the study on site to protect participants’ rights, assess compliance with the protocol, and ensure the ongoing implementation of appropriate data entry and quality control procedures.

### Statistical analysis

Continuous variables at baseline will be expressed as means plus/minus standard deviation and statistically tested using the two-sample *t* test or the Wilcoxon rank sum test. Categorical variables at baseline will be expressed as frequencies and statistically tested using the chi-squared test or Fisher’s exact test. If there is a significant difference between groups, the baseline variable will be considered as a covariate for efficacy analysis.

The full analysis set (FAS) will be analyzed primarily, including participants who take at least one dose of Palmijihwang-hwan and complete at least one pain assessment. Also, the per-protocol set (PPS) will be subordinately analyzed, including participants who take more than 80% of the total Palmijihwang-hwan dose and complete the trial. In the FAS analysis, the missing data will be imputed using the method of last observation carried forward. The primary outcome (change in the VAS score between baseline and endpoint) will be tested by analysis of covariance (ANCOVA) or rank ANCOVA (according to normality or homoscedasticity) with factors of group and study site and covariates of baseline values. Continuous variables for the secondary outcomes will also be tested, respectively, by ANCOVA or rank ANCOVA. Categorical variables for the secondary outcomes will be tested by chi-squared test or Fisher’s exact test according to the number of the cells with a value of 5 or less in the contingency table. Every variable predefined in the outcome sections will be compared at each time point, respectively.

The safety set will include participants who receive at least one dose of Palmijihwang-hwan. In safety analysis, the frequency and ratio of adverse events will be applied and compared between the treatment group and the control group using the chi-squared test or Fisher’s exact test. Any abnormal change in blood chemistry tests from visit 1 to 12 will be expressed as frequency and percentage and compared between the treatment group and the control group using McNemar’s chi-squared test, and any change in vital signs between visit 1 and 12 and between visit 1 and 13 will be expressed as change scores and compared between the treatment group and the control group using the two-sample *t* test or the Wilcoxon rank-sum test. Statistical tests will be carried out at 5% significance level (two-sided), using R software (Version 3.5.0 or later; R Foundation for Statistical Computing, Vienna, Austria).

For CEA, combination treatment with Palmijihwang-hwan with acupuncture will be compared with acupuncture alone from a healthcare system perspective. The treatment cycle will be assumed to be 10 weeks. The treatment period (i.e. analysis period) can be the average life span if we build a model for the data analysis. If not, it is impossible to extrapolate the observations to the patient’s life span. Therefore, this part is omitted as of now. For health-related outcomes, the RMDQ will be used for CEA and the EQ-5D for CUA. The absolute cost-effectiveness ratio will be estimated for the combination treatment of Palmijihwang-hwan with acupuncture and for acupuncture monotherapy. The cost-effectiveness of the combination therapy will be evaluated based on the incremental cost-effectiveness ratio. All economic analysis will be performed using TreeAgePro R 1.1 (Williamstown, MA, USA, 2018).

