### Interventions

#### Control group intervention

Participants in the control group will receive only the acupuncture treatment. Sterilized stainless steel needles with 0.25 mm width and 40 mm length (DB108C; Dongbang Medical Co., Boryung-si, South Korea) will be inserted at 11 local and 4 distal acupuncture points for 20 min. Acupuncture points are as shown in Table 1. Participants will receive the acupuncture treatment twice a week for 6 weeks, performed by Korean medical doctors who are specialists in acupuncture and moxibustion.

**Table 1 Tab1:** Acupuncture treatment protocol based on the Standards for Reporting Interventions in Clinical Trials of Acupuncture (STRICTA) [29]

1. Acupuncture rationale	1a) Acupuncture technique	Traditional Korean medicine theory
	1b) Reasoning for treatment provided (based on historical context, literature sources, and/or consensus methods), with where appropriate	Textbook of acupuncture and moxibustion and related articles
	1c) Extent of treatment variations	EX-B2 of lesion or upper and lower levels
2. Details of needling	2a) Number of needle insertions per subject per session	Acupuncture points: 15
	2b) Names of points used	Local acupuncture points: GV3, EX-B5/bilateral BL23, BL24, BL25, BL26 (total 11 points) Distal acupuncture points: bilateral BL40, BL60 (total 4 points)
	2c) Depth of insertion based on a specified unit of measurement	20–40 mm
	2d) Response sought	De-qi (penetrating, sharp, aching and painful sensations)
	2e) Needle stimulation	Rotation of the acupuncture needle 3–5 times
	2f) Needle retention time	20 min
	2 g) Needle type	Sterilized stainless steel needle with 0.25 mm width and 40 mm length (DB108C; Dongbang Medical Co., Boryung-si, South Korea)
3. Treatment regimen	3a) Number of treatment sessions	12 sessions
	3b) Frequency and duration of treatment sessions	Twice a week for six weeks (Total 12 times)
4. Other components of treatment	4a) Details of other interventions used for the treatment group	Lifestyle advice about chronic low back pain
	4b) Setting and context of treatment, including instructions to practitioners and information and explanations for patients	Practitioners are instructed to prevent talking with participants
5. Practitioner background	5) Description of participating acupuncturists	Korean medical doctors who are specialist in acupuncture and moxibustion at least three years of experience, or under supervision by a specialist

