#### Concomitant treatment

Other interventions including muscle relaxants, non-steroidal anti-inflammatory drugs (NSAIDs) (oral medication, topical application, or patch), antidepressant agents, anticonvulsants, treatments with Korean medicine (acupuncture, herbal medicine, and cupping), physical therapy, injections, or surgery will not be permitted during the treatment period (but are permitted during the follow-up period). However, concomitant medications taken within 4 weeks before trial participation or that are considered to have no effect on the interpretation of the results of this study may be allowed dependent on the judgment of the investigator.

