Furthermore, the features of this study such as the multicenter design and various outcome measures, including clinical relevance, quality of life, disability level, global assessment, and economic analysis, will improve the quality of the trial data and prevent bias. However, this study has several limitations. First, participants in the control group cannot be blinded because of the absence of a placebo, which could influence the study results. Second, we quoted Lee’s study for sample calculation but there is a difference in treatment duration. Participants in Lee's study [27] took Ojeok-san for 4 weeks, but this study needs participants to take Palmijihwang-hwan for 6 weeks. Third, there is no rescue therapy including drugs in the case of severe LBP, which could inhibit participants’ compliance. However, the results of this study will provide clinical evidence about the efficacy, safety, and CEA of Palmijihwang-hwan for treatment of CLBP, and this evidence will be useful for patients, physicians, researchers, and stakeholders.

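### The FAS, PPS and safety set are all defined by taking Palmijihwang-hwan, which the acupuncture-only control arm never receives, so the definitions contradict the planned efficacy and safety comparisons

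*Protocol article*

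**What the plan says.** All three definitions are in the Statistical analysis section of the protocol article.

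- **FAS**, the primary set: "including participants who take at least one dose of Palmijihwang-hwan and complete at least one pain assessment".
- **PPS**, the supporting set: "including participants who take more than 80% of the total Palmijihwang-hwan dose and complete the trial".
- **Safety set**: "The safety set will include participants who receive at least one dose of Palmijihwang-hwan".

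None of them gives a separate criterion for the control arm. Under Control group intervention the article states: "Participants in the control group will receive only the acupuncture treatment". The same Statistical analysis section tests the primary outcome by ANCOVA or rank ANCOVA "with factors of group and study site and covariates of baseline values". Adverse events are to be "compared between the treatment group and the control group using the chi-squared test or Fisher’s exact test", and changes in blood chemistry and vital signs are also compared between the two arms.

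**The concern.** The analysis sets decide who contributes to each result, and the FAS decides it for the primary outcome. A set that requires a dose of the experimental product cannot contain an arm that is never given it. The document therefore states a rule that its own analyses cannot follow.

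Anyone implementing the plan has to replace the rule with something else, and the article does not say what. The candidate replacements differ in whom they exclude. If the choice is left until data are available, it will be made in a trial where participants and practitioners know the allocation and the primary outcome is self-reported pain.

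**Working it through.** **1. The plan's own figure.** Inputs from Sample size calculation: changes of −26.41 (SD 19.06) and −12.83 (SD 19.45), two-sided alpha 0.05, power 0.80, 20% dropout.

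- Difference: 26.41 − 12.83 = 13.58.
- Pooled SD: √[(19.06² + 19.45²)/2] = 19.256.
- Standardised difference: 13.58 / 19.256 = 0.705.
- Two-sample t test (noncentral t): n = 32.55, rounded up to 33 per group. Power at 33 per group is 0.806.
- Dropout: 33 / (1 − 0.20) = 41.25, rounded up to 42 per group, 84 in total.

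The stated 33, 42 and 84 are reproduced. They assume two populated arms.

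**2. Can a control participant ever have a dose?**

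- Assigned treatment: no. Controls have acupuncture only (Design; Control group intervention).
- Permitted concomitant treatment: no. Under Concomitant treatment, "treatments with Korean medicine (acupuncture, herbal medicine, and cupping), physical therapy, injections, or surgery will not be permitted during the treatment period".
- A dummy dose that might count: no. The Discussion says "participants in the control group cannot be blinded because of the absence of a placebo".

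**3. The three rules applied to each arm as written.**

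| Set | Herb condition | Treatment arm | Control arm |
|---|---|---|---|
| FAS | at least one dose | at most 42 | 0 of 42 |
| PPS | more than 80% of doses | at most 42 | 0 of 42 |
| Safety | at least one dose | at most 42 | 0 of 42 |

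**4. Consequence for the planned tests.** With no controls, the group factor in the ANCOVA has one level, so the group effect cannot be estimated. The chi-squared and Fisher tables have an empty control column, and the two-sample tests on vital signs have no second sample.

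**5. Possible readings that restore the control arm.** Consider a participant in the treatment arm who is randomised, attends acupuncture and reports VAS scores, but never takes the herb.

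| Reading of the FAS | This participant | Control with the same visits and scores |
|---|---|---|
| Herb condition in treatment arm only | excluded | included |
| At least one dose or session of the assigned treatment | included | included |
| No treatment condition | included | included |

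Only the first reading excludes on a criterion that exists in one arm. Each such exclusion removes 1/42 = 2.4% of the planned treatment arm. The document gives no figure for how many participants might never start the herb, so neither the number nor the bias can be calculated.

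**6. After correction.** Up to 42 against 42 are available. The planned 33 against 33 evaluable keeps power at about 0.81, so the sample size need not change.

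**The case against.** The strongest reply is that the intention is plain. The Objectives and Design sections compare combination treatment with acupuncture alone, and the analysis section repeatedly compares the two groups, so no analyst would discard every control. That stands as far as it goes: the design is sound and an empty control arm is not a likely outcome. It does not show which correction was intended, and the primary set should be fixed before the data are seen.

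A reader might also draw three stronger conclusions that the document does not support.

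- **That no planned between-group comparison can be run.** The baseline tests in the Statistical analysis section and the cost-effectiveness and cost-utility comparison that follows are not tied to any of the three sets.
- **That the PPS ignores acupuncture adherence.** Withdrawal criteria makes compliance below 80% with either the herb or acupuncture a reason for withdrawal, and the PPS requires completion of the trial. A participant below the acupuncture threshold is therefore outside the PPS indirectly, in either arm. The link is only implicit.
- **That the primary analysis breaks randomisation.** This follows only if the herb condition is applied to the treatment arm alone. A condition on the assigned treatment in each arm is an equally natural reading, and the requirement for a pain assessment already applies to both arms.

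**Conclusion.** Wrong as written. The three definitions exclude all 42 planned controls and so contradict the FAS and PPS efficacy comparisons, including the primary ANCOVA, and the safety comparisons in the same section. This follows from the wording alone and needs no assumption about data. It is not detail left to a statistical analysis plan, because the article states the definitions explicitly.

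The practical harm is an undefined primary analysis set. Should the herb condition be applied to the treatment arm only, it becomes an arm-specific exclusion after randomisation and a possible source of bias. The size of that bias is unknown.

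**What to change.** Rewrite the three definitions before database lock.

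- **FAS:** all randomised participants with at least one pain assessment, analysed as randomised, with no condition on herb intake. The pain-assessment condition is the same for both arms and can stay.
- **PPS:** FAS participants who complete the trial and meet the protocol's existing compliance criterion for their assigned treatment, that is, acupuncture in both arms and the herb in the treatment arm only. A cross-reference to Withdrawal criteria makes the present indirect link explicit.
- **Safety set:** all participants who received at least one acupuncture session or one dose of the herb, analysed by treatment received.

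The cost is three sentences. No new data are needed and the sample size does not change. Trial status reports recruitment as ongoing, and Data management and quality control already describes how amendments are approved and published.

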### Procedure

The study schedule is as shown in Fig. 2. At the screening visit, patients who are interested in participation and who visit one of the four Korean medicine hospitals will be informed about the study. They will be also informed about expected benefits and risks and that they are able to withdraw from the study at any visit. If they sign the informed consent form voluntarily, the investigator will perform several examinations including check of vital signs, physical examination, spine x-ray, blood chemistry test, pregnancy test, and will collect demographic data, CLBP history, and concomitant treatment data, and apply the VAS, to determine the patient’s eligibility. If patients are eligible for the study but are taking medication, the investigator will determine the day of screening according to the participant’s medication to give a washout period. If the participant is taking anti-inflammatory medication or painkillers, the investigator will give a 2-week washout period. During the 6-week treatment, the participants in both groups will visit the hospital twice a week (total 12 visits) and receive acupuncture treatment at every visit. Participants in the treatment group will additionally receive Palmijihwang-hwan (at visit 1, 4, and 8) during the treatment period. Then, participants in both groups will be asked to complete a survey every 2 weeks (at visit 4, 8, and 12). On visit 13, 4 weeks after visit 12, all participants will visit the hospital for the final time.

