### Outcome measurement

#### Primary outcome

The primary outcome of this study will be change in the VAS score between baseline (visit 1) and completion of the intervention (visit 12) [30]. Using the 10-cm VAS (0, absence of pain; 10, the worst pain imaginable), the participants will be asked to report their degree of LBP.

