#### Secondary outcomes

#### The secondary outcomes are:

Pain: change in the VAS score between baseline (visit 1) and week 2 (visit 4), week 4 (visit 8), week 6 (visit 12), and 4 weeks after completion of the intervention (visit 13). Additional clinical relevance will be compared as follows;
Based on previous studies [31, 32], the proportion of the minimal clinically important difference (MCID) in CLBP is defined as a 2 cm decrease on the VAS. The proportion of MCID (more than 2 cm decrease on the VAS) between baseline and visit 4, 8, 12, and 13 will be recorded.The proportion of participants who experience more than 30% decrease on the VAS between baseline and visit 4, 8, 12, and 13.The proportion of participants who experience more than 50% decrease on the VAS between the baseline and visit 4, 8, 12, and 13.Disability: to evaluate the physical disability due to low back pain, the Roland and Morris Disability Questionnaire (RMDQ) will be applied [33]. The RMDQ score is calculated by 24 items (in the range 0 (no disability) to 24 (maximum disability)). Change in score in the Korean version of the RMDQ will be compared between baseline and visit 4, 8, 12, and 13.Quality of life: to evaluate quality of life, the EuroQol-5D (EQ-5D) questionnaire will be applied. The EQ-5D measures five dimensions (mobility, self-care, activities of daily life, pain, and anxiety/depression) using a 1–3 scale, and a VAS to rate the current health state using a 0–100 scale [34]; change in the EQ-5D scores between baseline and visit 4, 8, 12, and 13 will be compared.Global assessment: to evaluate participants’ impressions of change, the Patient Global Impression of Change (PGIC) will be applied at visit 12 and 13. The PGIC is measured on 7-point scale (from 1 (completely recovered) to 7 (vastly worsened)) with a score of 1–2 indicating improvement, 3–5 no change, and 6–7 deterioration [35].Economic analysis: to evaluate the intervention-related cost, CEA and cost-utility analysis (CUA) will be conducted. Cost data will be collected separately as follows;

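### As worded, the per-protocol set depends on completing the trial (visit 13), although the primary endpoint is measured at visit 12

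*Protocol article*

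**What the plan says.** All of the following is in the protocol article.

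- **Primary outcome section:** the endpoint is the "change in the VAS score between baseline (visit 1) and completion of the intervention (visit 12" (week 6).
- **Procedure:** "On visit 13, 4 weeks after visit 12, all participants will visit the hospital for the final time".
- **Secondary outcomes:** visit 13 is one of the time points for VAS change, the VAS responder proportions, RMDQ, EQ-5D and PGIC. It is described as "and 4 weeks after completion of the intervention (visit 13".
- **Statistical analysis, primary set:** "The full analysis set (FAS) will be analyzed primarily". Membership needs at least one dose of Palmijihwang-hwan and at least one pain assessment; nothing is required at visit 13. On missing values: "In the FAS analysis, the missing data will be imputed using the method of last observation carried forward".
- **Statistical analysis, PPS:** its role is stated as "the per-protocol set (PPS) will be subordinately analyzed". Its membership is then given by the clause "including participants who take more than 80% of the total Palmijihwang-hwan dose and complete the trial". One definition serves every endpoint and time point.
- **Withdrawal criteria:** loss to follow-up is listed with no time point attached.

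**The concern.** Whether the week 6 result was obtained per protocol is settled by what happened up to week 6. A completion rule that runs to week 10 lets a later event decide whether a measured week 6 value counts.

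That event may not be neutral. Participants know their allocation (Blinding), and treatments barred during the treatment period become permitted in follow-up (Concomitant treatment). Someone with poor relief at week 6 may seek other care and not return; someone who feels well may see no reason to return. Either pattern may differ between arms, so the rule can select on the outcome being compared. The documents do not show in which direction, or whether it will happen.

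The PPS also has a particular use here. Last observation carried forward is specified for the FAS only, so the PPS is the one analysis of the primary outcome named in the article without that imputation. It is the natural check on the FAS result and should not set aside observed primary data without need.

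**Working it through.** **1. What completion means.** The article does not define it, so the wording has to be compared.

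- Visit 12 is consistently described as completion of the intervention (Abstract, Primary outcome), and visit 13 is placed 4 weeks after that point (Secondary outcomes).
- The PPS sentence uses a different term and refers to the trial.
- Procedure makes visit 13 the final visit for all participants.
- The economic analysis assumes a 10-week cycle, which matches 6 weeks of treatment plus 4 of follow-up.

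The most natural reading is therefore completion through visit 13. Completion of the 12 treatment visits remains possible.

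**2. The plan's own figures reproduce.** Inputs from Sample size calculation: changes of −26.41 (SD 19.06) and −12.83 (SD 19.45), two-sided α 0.05, power 0.80, 20% dropout.

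- Difference: 26.41 − 12.83 = 13.58.
- Pooled SD: √((19.06² + 19.45²)/2) = 19.26.
- Standardised effect: 13.58/19.26 = 0.705.
- Noncentral t power: 0.793 at 32 per group and 0.8055 at 33, so 33 per group, as stated.
- Dropout: 33/0.8 = 41.25, rounded up to 42, as stated.

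**3. How many the visit 13 condition could remove.** No loss between visits 12 and 13 is given. Assumption: all of the planned 20% has been lost by visit 13, that is 0.20 × 42 = 8.4 per arm, and a share f of that loss falls after visit 12. Further assumptions: adherent controls count as members, and nobody is removed for poor adherence.

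- Kept under a visit 13 rule: 42 − 8.4 = 33.6 per arm.
- Kept under a visit 12 rule: 42 − 8.4 × (1 − f) per arm.
- Removed by the visit 13 condition: 8.4 × f per arm.

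| f | Kept, visit 12 rule | Removed by visit 13 condition | Power, visit 12 rule | Power, visit 13 rule |
|---|---|---|---|---|
| 0 | 33.6 | 0 | 0.806 | 0.806 |
| 0.25 | 35.7 | 2.1 | 0.829 | 0.806 |
| 0.5 | 37.8 | 4.2 | 0.849 | 0.806 |
| 0.75 | 39.9 | 6.3 | 0.868 | 0.806 |
| 1 | 42.0 | 8.4 | 0.891 | 0.806 |

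Power is by noncentral t with n rounded down. Under this assumption the visit 13 rule never falls below the planned 0.80. It removes nobody from the FAS.

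**4. The other half of the sentence.** PPS membership also requires more than 80% of the Palmijihwang-hwan dose. The control group receives acupuncture only (Control group intervention), so taken literally no control can qualify. The per-arm figures above hold only on the evident intent that adherent controls are included.

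**The case against.** The case against is substantial.

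- **The exclusion is inferred.** The article never says that completion means attending visit 13, and the full protocol or analysis plan may define it. This stands: a reader might infer that such participants will certainly be dropped, and the text does not go that far. It supports a most natural reading.
- **The primary analysis is untouched.** This also stands. A reader might infer that valid primary data are lost to the trial; in fact a measured visit 12 VAS does not drop out of the FAS because visit 13 is missed. It is also argued that any selection would show when PPS and FAS results are compared. That holds only in part: the two sets also differ in adherence and in imputation, so a gap between them could not be traced to visit 13.
- **Requiring completion is a usual per-protocol condition**, and visit 13 outcomes need visit 13 data. Both are true, but they justify the condition for visit 13 outcomes and not for a week 6 endpoint.
- **The size is not in the documents.** This stands. A reader might infer a shortfall in power by taking the 20% as lost by week 6 and continuing at the same rate: 1 − 0.8^(10/6) = 31% lost by week 10, 29.0 of 42 kept, power 0.75. No such attrition is stated anywhere. Loss may instead be concentrated before visit 12, when other treatments are barred and no rescue therapy is offered, a feature that the Discussion says could harm compliance. Nor does the article say that the sample size was set to power the PPS.

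**Conclusion.** The point holds as a minor fault of definition. As worded, and on the most natural reading, PPS membership for a week 6 endpoint depends on attendance at week 10, so adherent participants with an observed primary outcome can be left out of the PPS analysis because of a later event. The primary FAS analysis is not affected by this condition, and no stated figure is contradicted.

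The size cannot be determined from the article. If all of the planned 20% loss has occurred by visit 13, the number excluded lies between 0 and about 8 per arm, and power at the planned effect stays at about 0.81. The risk of selection is plausible because participants are unblinded, but it is not demonstrated. The point is worth raising because the remedy costs almost nothing and also settles an undefined term.

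**What to change.** Replace the single completion condition in the PPS definition with one matched to the endpoint:

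- primary outcome: adherence and a measured visit 12 VAS;
- other outcomes up to week 6: adherence and the measurement at the visit concerned;
- visit 13 outcomes: adherence and attendance at visit 13.

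In the same edit, state adherence for each arm, with acupuncture attendance as the measure for controls. Withdrawal criteria already contains an attendance condition that could be used, but its two parts must be reconciled first: 10 of 12 sessions is 83%, which is not below the 80% limit yet does not meet the requirement of more than 10 sessions. Repairing only the visit 13 wording would leave a set that, read literally, holds no controls.

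The cost is a sentence or two of analysis wording, with no new data and no change to conduct. The article reports recruitment as ongoing, so the wording should be settled before the data are analysed.

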### Sample size calculation

We performed sample size calculations to determine the appropriate number of participants. The purpose of this study is to verify the synergic effect of the combination treatment (acupuncture + Palmijihwang-hwan) compared to acupuncture treatment alone, using a visual analog scale (VAS) score for change between baseline and completion of the intervention (6 weeks). However, no study has been conducted to investigate the effects of Palmijihwang-hwan combined with acupuncture in the treatment of CLBP. Thus, we reviewed a similar study conducted in patients with CLBP [27] in which the authors evaluated the efficacy of a herbal formula, Ojeok-san, by measuring the VAS score change between baseline and completion of the intervention (4 weeks) and comparing this with the placebo group in randomized clinical trials of CLBP. In that study, the change in VAS score between baseline and completion of the intervention was − 26.41 ± 19.06 in the treatment group and − 12.83 ± 19.45 in the control group. Based on these data, 33 participants would be required per intervention group for a two-arm study and a two-tailed test with 0.80 power (1-β) at the 0.05 α level, as calculated using G* Power (Version 3.1.9.3) [28]. After assuming a 20% drop out rate, we calculated that we would need to recruit 42 participants per group. Thus, a total of 84 participants will be required.

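### Last observation carried forward (LOCF) in the primary analysis can bias the week-6 VAS difference, in either direction, when dropout or the improvement still to come differs between arms

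*Protocol article*

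**What the plan says.** The primary outcome is the VAS change from visit 1 to visit 12 (week 6). The Statistical analysis section tests it in the FAS by ANCOVA, or rank ANCOVA if assumptions fail, "with factors of group and study site and covariates of baseline values". For gaps in that set it gives one rule: "In the FAS analysis, the missing data will be imputed using the method of last observation carried forward". The rule is not limited to visit 12, and the same section compares every outcome at each time point, so as worded it also fills visit 13.

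To enter the FAS a participant must, among other things, "complete at least one pain assessment". This is not stated to be a post-baseline assessment. The only other efficacy set is the per-protocol set, "including participants who take more than 80% of the total Palmijihwang-hwan dose and complete the trial".

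Three other places bear on the rule:

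- **Sample size calculation:** 33 per group becomes 42 "After assuming a 20% drop out rate".
- **Secondary outcomes and Procedure:** VAS change is assessed at visits 4, 8 and 12 (weeks 2, 4 and 6), so interim values exist.
- **Withdrawal criteria:** compliance below 80% with the herbal doses or with acupuncture is a reason for withdrawal. The herbal part can apply only to the treatment arm.

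**The concern.** LOCF assumes that someone who leaves after week 2 or week 4 would have had the same pain at week 6. If pain is still changing, the filled value misses the rest of that change. What matters for the comparison is whether the missed amount differs between arms. It differs if dropout rates differ, or if the arms have different amounts of improvement still to come. The sample size calculation itself assumes unequal improvement.

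Unequal dropout is plausible from the protocol's own text. The treatment arm has an additional route to withdrawal, participants are not blinded, and the Discussion notes that the lack of rescue therapy could affect compliance.

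The filled value also enters the model as if it had been measured, so the standard error carries no uncertainty for the imputation. The per-protocol set does not test the assumption, because it is restricted to adherent completers. At stake is the primary effect estimate, which could be diluted or exaggerated without the planned efficacy analyses showing it.

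**Working it through.** **Inputs from the Sample size calculation.** Changes of −26.41 (SD 19.06) and −12.83 (SD 19.45), two-sided α 0.05, power 0.80, 20% dropout. I read these VAS figures as mm on a 100-mm scale.

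**The plan's own figure.** Difference = 26.41 − 12.83 = 13.58. Pooled SD = √((19.06² + 19.45²)/2) = 19.26. Standardised effect = 13.58/19.26 = 0.705. The noncentral t calculation gives 32.55, so 33 per group; 33/(1 − 0.20) = 41.25, so 42 per group and 84 in total. The plan's numbers are reproduced.

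**Expected LOCF estimate.** Let d be the dropout proportion in an arm and f the mean fraction of the week-6 change reached at the last observation. With dropout unrelated to outcome,

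expected LOCF change = true change × (1 − d + d·f).

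The protocol gives neither f nor d by arm, so both are assumptions. With 1:1 allocation, each split below averages to the planned 20%.

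- *Linear course, last seen at week 2 or 4 with equal chance:* f = (1/3 + 2/3)/2 = 0.5.
- *Early plateau, 60% of the change by week 2 and 90% by week 4:* f = (0.6 + 0.9)/2 = 0.75.
- *Linear course, baseline also carried with equal chance:* f = (0 + 1/3 + 2/3)/3 = 1/3.
- *Flat after week 2:* f = 1.

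Example, linear, 30% treatment/10% control: 26.41 × 0.85 − 12.83 × 0.95 = 22.45 − 12.19 = 10.26 mm.

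| Course | 20%/20% | 30% treatment/10% control | 10% treatment/30% control |
|---|---|---|---|
| Linear | 12.22 (−10%) | 10.26 (−24%) | 14.18 (+4%) |
| Early plateau | 12.90 (−5%) | 11.92 (−12%) | 13.88 (+2%) |
| Linear, baseline also carried | 11.77 (−13%) | 9.15 (−33%) | 14.39 (+6%) |
| Flat after week 2 | 13.58 (0) | 13.58 (0) | 13.58 (0) |

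**When the direction turns.** With the same f in both arms, the change missed is d(1 − f) × true change. The bias is zero when 26.41·d(treatment) = 12.83·d(control), that is, when control dropout is 26.41/12.83 = 2.06 times treatment dropout. Below that ratio LOCF shrinks the effect; above it LOCF exaggerates it.

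**Power and type I error.** Simulation with 20,000 runs, 42 per arm, SD 19.26 at each visit, assumed correlation 0.6 between visits, linear course, random dropout and a t test on change:

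- *Planned effect:* power 0.89 without dropout, 0.80 at 20%/20%, 0.64 at 30%/10% and 0.90 at 10%/30%.
- *No true effect, both arms improving by 12.83:* no bias and about 5% rejection at 20%/20%. At 30%/10% or 10%/30% there is a spurious difference of 12.83 × (0.95 − 0.85) = 1.28 mm and about 6% rejection.
- *No true effect, both arms improving by 26.41:* a spurious 2.64 mm and about 9% rejection at the unequal splits. If baseline is also carried, the rejection rates rise to about 7% and 13%.

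**Dropout related to pain.** When leaving is made more likely by worse visit-4 pain (SD 1.9 cm, linear course), two separate simulations against a true −1.36 cm gave −1.22 cm at 20%/20% and −1.01 and −0.99 cm at 30%/10%. The mean bias is similar to the random-dropout case.

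**The case against.** The strongest reply is that the size rests on things the protocol does not say. It gives no course of pain between visits and no dropout by arm. Its planning data are a single 4-week change from a placebo-controlled trial of another herbal formula. This stands, and it is why the result is a range: an early plateau halves the loss, and a flat course removes it when dropout is unrelated to outcome.

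Some stronger readings are tempting but not supported:

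- *LOCF biases the result whenever pain is still improving or dropout differs.* If both arms share the same course and the same dropout, the missed change cancels.
- *The false-positive rate is inflated in general.* With equal dropout it is not.
- *LOCF is at least conservative.* The 10%/30% split exaggerates the effect.
- *The trial becomes underpowered at its planned dropout.* Under random dropout of 20% in each arm, simulated power is still 0.80, because 42 per arm remain in the analysis. Pain-related dropout with linear improvement gave 77%.
- *The protocol is deficient for giving no delta-type sensitivity analysis.* That may sit in an analysis plan that is not shown. The point here is the primary method, which the article does fix.

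The power figures come from a t test, or a two-group regression for the pain-related runs, not from the planned ANCOVA with site and baseline. A missing-at-random method recovers the true value in a simulation built on that assumption, so such recovery does not show that the assumption holds here. Lastly, participants may be withdrawn for low compliance or unpermitted treatment, and a mixed model then estimates their pain as if they had continued. That is a choice of target and has to be stated.

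**Conclusion.** The concern holds in a bounded form. The protocol fixes LOCF as the primary missing-data method while expecting 20% dropout and giving the treatment arm an extra route to withdrawal. Nothing in the document offsets this.

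If dropout averages 20% and pain is still improving, the estimate of a true 13.58 mm difference ranges from about 10.3 to 14.2 mm on a linear course and from about 11.9 to 13.9 mm with an early plateau, depending on which arm loses more participants. If the last carried value can be the baseline one, the range widens to 9.2–14.4 mm. With no true effect and 30%/10% dropout, type I error is roughly 6–9% when only post-baseline values are carried.

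These figures rest on assumed courses and dropout splits. They show what the rule can do, not what it will do in this trial. The sample size is sound and is not in question.

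**What to change.** Replace LOCF in the primary visit-12 analysis by one of two methods:

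- a mixed model for repeated measures on VAS change at visits 4, 8 and 12, with group, visit, group-by-visit, site, baseline VAS and baseline-by-visit, an unstructured covariance, and the visit-12 group contrast as the primary test; or
- multiple imputation using the interim VAS values, followed by the planned ANCOVA with group, site and baseline.

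State that the missing-at-random target is the outcome had withdrawn participants continued. Reword the switch to rank ANCOVA so that it fits the method chosen. Analyse visit 13 separately, because the Concomitant treatment section permits other treatments during follow-up and an on-treatment value should not stand in for that period. Keep LOCF only as a sensitivity analysis.

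The cost is an amendment to the analysis text, slightly more programming in R, and an explicit missing-at-random assumption that cannot be verified from the data. No new data are needed and the total stays at 84. The article reports recruitment as ongoing and describes a route for amendments, so the change could be made before the analysis.
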